#### Safety evaluation

To evaluate the safety of the intervention and overall protocol, we will record adverse events such as burns to the skin, prolonged abnormal cutaneous sensation, dizziness, fatigue, and pain related to overuse of the affected arm. To monitor the existence of the temporary side effects, especially of the tDCS, we will provide participants with a questionnaire [58] after every 20 min of active or sham tDCS intervention. The questionnaire consists of 14 items regarding symptoms which will enable us to determine if the participants are experiencing severe symptoms. The score ranges from 1 to 10, from absent to severe symptoms.

#### Clinical outcomes

The schedule of data collection is summarized in SPIRIT figure (Fig. 4). Clinical assessments of the upper limb and neurophysiological and neuroanatomical assessments will be conducted prior to the intervention (baseline, t_0_), at the middle of the intervention [middle, t_1_ (ARAT only)], immediately after the intervention (post, t_2_), and 1 month after the intervention (follow-up, t_3_).

**Fig. 4 Fig4:**
[figure not shown]
SPIRIT figure. tDCS, transcranial direct current stimulation; MMSE, Mini-Mental State Examination; FIM, functional independence measure; ARAT, Action Research Arm Test; FMA, Fugl-Meyer assessment for the upper extremity; MAL-14, Motor Activity Log-14; CBI, cerebellar brain inhibition; MEP, motor-evoked potential; MRI, magnetic resonance imaging

The effects of the interventions will be assessed using ARAT, Fugl-Meyer Assessment (FMA) for the upper extremity, and Motor Activity Log-14 (MAL-14). ARAT is a clinical measurement that consists of 19 tests with 4 subscales: grasp, grip, pinch, and gross movement, which assess upper limb motor function [59, 60]. The quality of movement is scored on an ordinal 4-point scale, ranging from 0 to 3 in each test, with a maximum score of 57 [59]. ARAT is classified as an outcome measurement of activity capacity [61, 62] based on the International Classification of Functioning framework [63], and it shows excellent validity and reliability in chronic stroke patients [64]. FMA is classified as an outcome measurement of body functions [62] based on the International Classification of Functioning framework [63]. FMA for the upper extremity consists of 33 items including reflex testing, movement observation, grasp testing, and coordination assessment. The score ranges from 0 to 66. FMA shows excellent validity and reliability in chronic stroke patients [64, 65]. MAL-14 is a structured interview to assess how much (amount of use: AOU) and how well (quality of movement: QOM) a patient uses the paretic hand and arm during activities of daily living [66, 67]. For the AOU assessment, the score ranges from 0 (never uses the arm) to 5 (uses the arm as often as before the stroke), while for the QOM assessment, the score ranges from 0 (never uses the arm) to 5 (uses the arm as well as before the stroke). MAL-14 is classified as an outcome measurement of activity performance [61, 62] based on the International Classification of Functioning framework [63], and it shows excellent validity and reliability in chronic stroke patients [68].

ARAT and FMA will be video-recorded [69], and video-based assessments will be conducted by two trained occupational therapists who will be blinded to the allocation and will not be involved in the interventions. In addition, the following participant baseline characteristics will be collected: age, the affected side of the brain, time since onset, and FIM and MMSE scores.

#### Neurophysiological assessments

As an index of cerebellar excitability, we will assess the magnitude of cerebellar inhibition (CBI) to the contralateral M1 using a paired-pulse TMS paradigm (Magstim 200^2^, Magstim Company, Whitland, UK) (Fig. 5). CBI will be measured by delivering a conditioning stimulus (CS) over the cerebellum for 5 ms prior to a test stimulus (TS) over M1, resulting in the reduction of motor evoked potential (MEP) elicited by TS over M1 [70]. CBI is thought to be driven by inhibitory outputs from the cerebellar cortex to the deep cerebellar nuclei that have excitatory outputs to the contralateral M1 [71]. Therefore, changes in CBI magnitude can be interpreted as cerebellar excitability changes [72, 73]. We will assess the cerebellar excitability changes with the assumption that cerebellar plasticity may underlie the intervention effects.

**Fig. 5 Fig5:**
[figure not shown]
Position of the TMS coils for measuring CBI and MEP. A figure-of-eight coil will be placed over the ipsilesional side of M1 to deliver the test stimuli for eliciting MEP in the FDI muscle. A double-cone coil will be placed over the contralesional side of the cerebellum to deliver the CS. The CS will be delivered 5 ms prior to the TS. CBI will be calculated as the ratio between the peak-to-peak amplitude of the conditioned MEP (black line) and the unconditioned test MEP (grey line). MEP, motor-evoked potential; FDI, first dorsal interosseous; TS, test stimulation; CS, conditioning stimulation; M1, primary motor cortex; CBI, cerebellar brain inhibition; CB, cerebellum

The CS will be delivered to the contralesional side of the cerebellum using a double-cone coil which will be centered at the same location determined by the computation modeling, while the TS will be delivered to the ipsilesional side of M1 using the figure-of-eight coil over the optimal stimulation site (“hot spot”) of the first dorsal interosseous (FDI) muscle (Fig. 5). To determine the intensity of the cerebellar CS, we will first test the brainstem active motor threshold for the pyramidal tract by delivering stimuli over the inion using a single pulse with the double-cone coil. The brainstem active motor threshold is defined as the nearest 5% maximum stimulator output (MSO) that elicits MEPs exceeding 50 μV from the FDI muscle in the affected hand in at least 5 of 10 successive stimuli [74]. The cerebellar CS intensity will be set at 5% below the brainstem active motor threshold [70, 75, 76]. If the threshold is not observed below 80% of MSO, 70% of MSO will be used for the cerebellar CS. For the intensity of TS over M1, we will first assess the resting motor threshold (rMT) of the FDI muscle which is determined as the lowest intensity that evokes an MEP amplitude greater than 50 μV in at least 5 of 10 successive stimuli [74]. Thereafter, the TS intensity will be set at 125% of rMT. For the CBI assessment, in a set of 30 TS, 15 TS will be combined with the preceding CS (conditioned TS), while the other 15 TS will be delivered without CS (unconditioned TS). The inter-stimulus interval for TS will be 4–6 s, and the order of conditioned and unconditioned TS will be randomized. The position of the TS over M1 will be tracked using a neuronavigation system (Brainsight, Rogue Research, Montreal, Canada). CBI will be calculated as the ratio of the mean amplitude of conditioned MEP over the unconditioned MEP.

We will also assess M1 excitability by delivering single-pulse TMS over the ipsilesional M1 as a separate measurement set to confirm that potential CBI changes will not be accompanied by M1 excitability changes. For this purpose, 15 stimuli with an intensity of 125% of rMT will be applied with the inter-stimulus interval of 4–6 s. The mean amplitude will be used as a proxy for M1 excitability.

Surface electromyography will be recorded using a biosignal recording system (Nuropack X1 MEB-2312; Nihon Kohden Corporation, Tokyo, Japan) at the frequency of 5 kHz, with a bandpass filter of 10 Hz to 10 kHz. Recorded analog data will be digitized with a micro 1401 AD converter (Cambridge Electronic Design, Cambridge, UK) and stored on a computer (Signal Software, Cambridge Electronic Design, Cambridge, UK) for offline analysis.

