#### Analytical methods

The feasibility outcomes will be reported with descriptive statistics. Recruitment, enrollment, adherence, and retention rates will be calculated with a 95% confidential interval. Furthermore, adverse events and their frequency will be recorded. If there are some exclusions or dropouts, the reasons and the step at which they occur will be recorded. For the potential side effects of tDCS, the median score for every 14 items of the questionnaire regarding symptoms will be calculated. Regarding the success of blinding, the percentage of correct guesses will be reported.

The active and sham tDCS groups will be compared with regard to demographic variables to assess group differences using the Student’s *t* test or Mann-Whitney *U* test for continuous variables and the *χ*^2^ test for categorical variables. Group differences of the ARAT, FMA, and MAL-14 scores and neurophysiological measures outcomes will be analyzed using multivariable regression analyses and compared at each assessment time point. To evaluate the efficacy of the present pilot study, an effect size of the ARAT score will be computed, which will be used to determine the sample size for the future main trial.

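### The M1 check uses MEP amplitude at 125% of rMT, which is largely insensitive to threshold shifts if rMT is re-measured at each visit, so it cannot alone support a statement that M1 excitability is unchanged

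*Protocol article*

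**What the plan says.** All of the measurement text is in the Protocol article, section Neurophysiological assessments.

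- **Purpose.** A single-pulse set over ipsilesional M1, separate from the CBI block, is included "to confirm that potential CBI changes will not be accompanied by M1 excitability changes".
- **Intensity.** In that set, "15 stimuli with an intensity of 125% of rMT will be applied with the inter-stimulus interval of 4–6 s".
- **Read-out.** "The mean amplitude will be used as a proxy for M1 excitability". No other M1 proxy is named.
- **Threshold.** rMT is "determined as the lowest intensity that evokes an MEP amplitude greater than 50 μV in at least 5 of 10 successive stimuli".
- **Order of steps.** For the CBI test stimulus, "we will first assess the resting motor threshold (rMT) of the FDI muscle". The next step is "Thereafter, the TS intensity will be set at 125% of rMT".

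The Clinical outcomes section places the neurophysiological assessments at t0, t2 and t3; t1 is for the ARAT only. Under Analytical methods, "neurophysiological measures outcomes will be analyzed using multivariable regression analyses and compared at each assessment time point". The text does not name rMT as an outcome, and it does not say that the absolute intensity used at t0 is carried forward to later visits.

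**The concern.** By the protocol's own definition, rMT is a measure of corticospinal excitability: it is the intensity needed to reach a fixed small response. Setting the stimulus as a multiple of rMT rescales the input to the quantity that the check is meant to measure. If M1 becomes more excitable through a lower threshold, the stimulus is lowered in proportion, and the MEP may stay the same or even fall.

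The inference from CBI to cerebellar excitability is the protocol's stated mechanistic reading, and the separate M1 set is the stated safeguard for it. If that set shows no change, the report could say that M1 excitability did not change when its threshold had. The risk applies to within-person readings from t0 to t2 or t3, where two weeks of intensive training of the affected arm make an M1 change plausible. It also applies to any M1 effect specific to active tDCS.

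**Working it through.** The documents give no figure for this check, so there is nothing to reproduce. The working shows how the read-out responds to a threshold shift.

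**Inputs from the protocol:** intensity 125% of rMT; rMT defined at 50 μV; visits t0, t2 and t3; mean MEP as the only M1 proxy.

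**Assumed, not in the documents:** a sigmoid recruitment curve, MEP(I) = Mmax / (1 + exp((S50 − I)/k)), with Mmax = 2 mV; the baseline rMT values; and the size of the threshold change.

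**Algebra.** The MEP depends on the exponent (S50 − I)/k.

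- *Curve scales with threshold* (S50 = a·rMT, k = b·rMT). At I = 1.25·rMT the exponent is (a − 1.25)/b. rMT has dropped out, so the change is exactly zero.
- *Curve shifts in parallel* (S50 = rMT + d, k constant). At I = 1.25·rMT the exponent is (d − 0.25·rMT)/k. A fall of Δ in rMT raises the exponent by 0.25Δ/k, so the MEP falls. At a fixed intensity the same shift lowers the exponent by Δ/k, so the MEP rises. On this scale the rescaled check responds with a quarter of the size and the opposite sign.

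**Example 1.** rMT falls from 50% to 45% of MSO. Scaled curve: S50 = 1.3·rMT, k = 0.08·rMT. Parallel curve: S50 = rMT + 15, k = 4. Both give about 46 μV at rMT, close to the protocol's 50 μV. The baseline intensity is 1.25 × 50 = 62.5% of MSO, and the baseline MEP is 2/(1 + exp(2.5/4)) = 0.697 mV.

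| Intensity after the fall | Scaled curve | Parallel curve |
|---|---|---|
| 125% of current rMT (56.25% of MSO) | 2/(1 + exp(2.25/3.6)) = 0.697 mV (0%) | 2/(1 + exp(3.75/4)) = 0.563 mV (−19%) |
| Fixed t0 intensity (62.5% of MSO) | 2/(1 + exp(−4/3.6)) = 1.505 mV (+116%) | 2/(1 + exp(−2.5/4)) = 1.303 mV (+87%) |

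**Example 2, other parameters.** Baseline k = 5% of MSO, rMT exactly at 50 μV, baseline rMT 45, 55 or 65% of MSO.

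| Change in M1 | 125% of current rMT | Fixed t0 intensity |
|---|---|---|
| rMT falls 10% | 0% (scaled); −17% to −19% (parallel) | +78% to +135% |
| rMT rises 10% | 0% (scaled); +19% to +21% (parallel) | −54% to −67% |
| Mmax rises 50% (rMT falls about 2 points of MSO) | −3% to +7% | not computed |
| k falls 20%, rMT unchanged (steeper slope) | +50% to +55% | same stimulus, same result |

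The check as written is therefore nearly silent, or points the wrong way, for threshold shifts. It still responds clearly to a slope change at constant rMT.

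**The case against.** **The CBI ratio is not left unguarded.** A reader might infer that an undetected change in test-MEP size could distort the CBI ratio and be reported as cerebellar plasticity. The documents do not support that. The CBI test stimulus and the separate M1 set use the same 125% of rMT over the same ipsilesional M1, so a change in test-MEP size would also appear in the M1 set. In the scaled case neither changes; in the parallel case both fall by 19%. As a control on test-MEP size the set works, and tying the test stimulus to current rMT is reasonable for the ratio.

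**Training common to both arms.** A reader might also infer that training-induced M1 change biases the active-sham comparison. Both arms receive the same training, so a shared shift does not by itself create a group difference.

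**The check is not blind to all M1 change.** Slope changes at unchanged rMT are visible, so calling the check invalid would go too far.

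**Re-measurement is inferred.** The article gives the order of steps but does not say that rMT is re-determined at t2 and t3. If the t0 value is carried forward, the point falls away. Re-determination is the natural reading, because finding rMT is a step of an assessment done at all three visits and nothing limits it to baseline.

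**The sizes are illustrative.** The exact 0% follows from assuming that the whole curve scales with rMT. This is granted; the parallel-shift case does not share that feature and leads to the same conclusion.

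All five objections stand, and they narrow the point. None of them rescues the specific claim that M1 excitability is unchanged.

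**Conclusion.** The point holds in limited form. If rMT is re-determined at each visit, mean MEP at 125% of rMT cannot by itself support the statement that M1 excitability did not change, because a threshold shift is cancelled or slightly reversed: about 0% to −19% for a 10% fall in rMT under the assumed curves, against about +78% to +135% at the fixed t0 intensity. The percentages depend on assumed curve shapes; the weak or reversed response follows from the rescaling in both curve families tried.

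What is affected is the mechanistic reading of CBI within persons and the detection of any tDCS-specific M1 effect. The feasibility outcomes, the progression criteria and the ARAT effect size are not affected. Separately, the word confirm promises more than the design can give: the article states no margin for no change, and there are only 12 participants per group.

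**What to change.** 1. State whether rMT is re-determined at t0, t2 and t3.
2. Analyse rMT (% MSO) at those visits as an M1 excitability outcome beside MEP amplitude.
3. At t2 and t3, deliver the separate 15-pulse set at the participant's absolute t0 intensity, that is, 125% of the t0 rMT in % MSO. Leave the CBI test stimulus at 125% of current rMT.
4. Replace confirm with assess in the statement of purpose.

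The cost is small. rMT is already measured, and no pulses, visits or equipment are added; one stimulator setting changes in an existing block. Little is lost, because the 15 unconditioned pulses in the CBI block already give the MEP at 125% of current rMT. The downside is that MEPs may be small at the t0 intensity if a participant's rMT rises, which is itself informative. Item 3 needs to be settled before data collection, since fixed-intensity responses cannot be recovered at analysis; items 2 and 4 can be applied at any stage before the analysis.

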### Randomization

Participants will be stratified according to age and ARAT score and randomly allocated to either the active tDCS or sham tDCS group using a computer-generated, permuted block randomization method with permuted block sizes of 2 and 4. The random allocation will be conducted using the Research Electronic Data Capture (REDCap) tools [40] by independent researchers who will not be involved in any intervention and assessments.

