#### Sample size

A previous study proposed the rules of thumb for estimating the sample size of a pilot study based on the anticipated effect size of the future main trial [79]. According to the proposal, if the future main trial is designed around medium to large effect with 80% power and a two-sided 5% significance, a sample size for the pilot trial is set at 10 in each group [79]. Allowing for a 20% of drop-out rate, we will recruit 12 participants in each group.

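### The M1 excitability check is meant to confirm that nothing changed, but a group-difference regression with 10 to 12 patients per arm cannot show that

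*Protocol article*

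**What the plan says.** In the Protocol article, under Neurophysiological assessments, cerebellar brain inhibition (CBI) is the ratio of conditioned to unconditioned MEP amplitude. A change in CBI is to be interpreted as a change in cerebellar excitability. A second, separate set of 15 single pulses over the ipsilesional M1 at 125% of resting motor threshold is added "to confirm that potential CBI changes will not be accompanied by M1 excitability changes". Its endpoint is simple: "The mean amplitude will be used as a proxy for M1 excitability".

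Under Analytical methods, group differences in the clinical scores and the "neurophysiological measures outcomes will be analyzed using multivariable regression analyses and compared at each assessment time point". That is the only analysis the article gives for the M1 measure. The same section commits to 95% intervals for the feasibility rates.

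Under Sample size, "a sample size for the pilot trial is set at 10 in each group", taken from a published rule of thumb for pilot trials, and then: "Allowing for a 20% of drop-out rate, we will recruit 12 participants in each group". Under Clinical outcomes, the middle assessment is restricted, "at the middle of the intervention [middle, t_1_ (ARAT only", so the M1 comparisons after treatment are at t2 (post) and t3 (1-month follow-up).

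**The concern.** The stated purpose of the M1 set is to show that something did not happen. A regression that estimates and tests a group difference can find an M1 change. Failing to find one shows absence only if the estimate is precise enough to exclude a change that matters. With 10 to 12 per arm it is not.

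What is at stake is how any CBI finding is interpreted. Test pulses for CBI are delivered over the same M1, and the separate M1 set is there as a safeguard on attributing a CBI change to the cerebellum. If a null M1 result were reported as the promised confirmation, the safeguard would often appear to pass even when M1 had changed. The problem is independent of how well MEP amplitude measures M1 excitability; it would remain with a perfect measure.

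**Working it through.** **Inputs from the article.** 10 per arm before the drop-out allowance; 20% drop-out; 12 per arm recruited.

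**Inputs assumed, because the article gives none for this measure.** Two-sided alpha of 0.05 (the article's "80% power and a two-sided 5% significance" refers to the future main trial); a true M1 group difference of 0.5 SD, with 0.8 SD for comparison; a baseline-to-outcome correlation r of 0.3 to 0.8 if the regression adjusts for baseline.

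**Step 1, the plan's own figure.** 10 × 1.2 = 12, which matches the stated number. Dividing instead gives 10 / 0.8 = 12.5, or 13. The base of 10 rests on the cited rule and cannot be derived from the article. The checks below use n = 10 and n = 12 per arm.

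**Step 2, chance of a non-significant result, unadjusted.** Two-sample t test, df = 2n − 2, noncentrality = d × √(n/2).

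| n per arm | d | noncentrality | power | non-significant |
|---|---|---|---|---|
| 12 | 0.5 | 1.22 | 21.6% | 78.4% |
| 10 | 0.5 | 1.12 | 18.5% | 81.5% |
| 12 | 0.8 | 1.96 | 46.6% | 53.4% |
| 10 | 0.8 | 1.79 | 39.5% | 60.5% |

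The difference detectable with 80% power is about 1.20 SD (n = 12) or 1.32 SD (n = 10).

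**Step 3, the same with baseline adjustment.** Residual SD = √(1 − r²), df = 2n − 3, true difference 0.5 raw SD.

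| r | residual SD | non-significant, n = 12 | non-significant, n = 10 |
|---|---|---|---|
| 0.3 | 0.954 | 76.8% | 80.2% |
| 0.5 | 0.866 | 72.9% | 77.0% |
| 0.7 | 0.714 | 62.7% | 68.5% |
| 0.8 | 0.600 | 50.5% | 58.0% |

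**Step 4, precision, which does not depend on the assumed effect.** Expected 95% half-width = t(0.975) × residual SD × √(2/n).
- Unadjusted, n = 12: 2.074 × 0.408 = 0.85 SD.
- Unadjusted, n = 10: 2.101 × 0.447 = 0.94 SD.
- With r = 0.7: 0.61 SD (n = 12) and 0.67 SD (n = 10).
- With r = 0.8: 0.51 SD (n = 12) and 0.57 SD (n = 10).

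At these expected widths, even an estimate of exactly zero would leave a half-SD M1 difference inside the interval.

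**Step 5, would a margin rescue the claim?** Take an illustrative equivalence margin of ±0.5 SD, a true difference of zero, and two one-sided 5% tests. The number needed for 80% power is 2 × ((1.645 + 1.282)/0.5)², about 69 per arm. At 12 and 10 per arm the chance of meeting the margin is about 0.2% and 0.1% unadjusted, and 8.9% and 4.2% with r = 0.7.

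**The case against.** **No rule says that non-significance means no change.** This stands. The article gives no alpha, p-value rule or decision rule for the M1 measure. That reading is inferred from the verb in the purpose clause.

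**A margin or interval rule could sit in an analysis plan that is not shown.** Possible, and its absence from an article is not the point. The point is that the stated aim exceeds what the stated analysis and numbers can deliver. Step 5 shows that a margin of half an SD would almost never be met at this size; a wider one would be met more often but would leave a large M1 change open.

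**The 80% figure is not a property of the planned analysis.** This stands in part. It needs an unadjusted test, an assumed alpha and an assumed 0.5 SD. The planned analysis is multivariable, and with baseline adjustment the range is roughly 50 to 80%.

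**Stronger consequences do not follow.** A reader might infer that the pilot will probably report a mechanism specific to the cerebellum. That also requires a CBI change to be found, with the same small numbers. For one visit, with the two tests taken as independent and M1 changed by 0.5 SD, a significant CBI result together with a non-significant M1 result has probability 0.216 × 0.784 = 17% (n = 12) or 0.185 × 0.815 = 15% (n = 10) if the CBI effect is 0.5 SD, and 37% or 32% if it is 0.8 SD. A reader might also infer that the claim would carry into the main trial. The progression criteria are enrolment, recruitment, adherence and retention, and the main-trial sample size uses the ARAT effect size. M1 excitability enters neither.

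**The CBI interpretation does not rest on this check alone.** Also fair. The article supports it with cited physiology, and each CBI ratio carries its own unconditioned MEP from the same randomised set. The separate M1 set is an additional safeguard.

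**Conclusion.** The concern holds in a limited form. The article states that the M1 set will confirm an absence, and the analysis and sample size it gives cannot support that conclusion. Under a two-sided 5% test and a true 0.5 SD difference, both assumed, a real M1 change goes undetected in about 80% of trials unadjusted and in roughly 50 to 80% with baseline adjustment at r between 0.8 and 0.3. The precision result needs no assumed effect: the unadjusted 95% half-width is 0.85 to 0.94 SD, so a null result would leave a large M1 change open.

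The documents do not support saying that a null result will be read as confirmation. The weight is modest: this is a mechanistic check within a feasibility pilot. It is still worth correcting, because it governs what the trial may say about M1 and about the specificity of any CBI change.

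**What to change.** 1. Under Neurophysiological assessments, replace "to confirm that potential CBI changes will not be accompanied by M1 excitability changes" with: *to estimate any accompanying change in M1 excitability*.
2. Under Analytical methods, add: *The between-group difference in M1 MEP amplitude at t2 and t3, adjusted for baseline, will be reported with its 95% confidence interval. A non-significant result will not be taken as evidence that M1 is unchanged or that a CBI change is specific to the cerebellum.*

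A formal equivalence rule is optional. No margin can be derived from the article, and with a margin of about half an SD it would rarely be met at this sample size.

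The cost is two small wording changes, with no new data, visits or patients. The downside is a weaker claim: the pilot will usually have to report M1 involvement as undetermined.

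### The stated EMG settings do not fit together: 5 kHz recording with a pass-band up to 10 kHz, four times the Nyquist limit, admits noise that can bias MEP and CBI measures by an amount the protocol does not let us fix

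*Protocol article*

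**What the plan says.** All of this is in the protocol article, under Neurophysiological assessments and the Fig. 5 caption.

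- **Recording:** surface EMG is taken "at the frequency of 5 kHz, with a bandpass filter of 10 Hz to 10 kHz". The next sentence adds: "Recorded analog data will be digitized with a micro 1401 AD converter". No separate rate is given for that converter, and no anti-alias or digital low-pass filter is mentioned.
- **Amplitude measure:** the Fig. 5 caption makes it peak-to-peak: "CBI will be calculated as the ratio between the peak-to-peak amplitude of the conditioned MEP", relative to the unconditioned response.
- **CBI:** "CBI will be calculated as the ratio of the mean amplitude of conditioned MEP over the unconditioned MEP".
- **Thresholds:** the resting motor threshold and the brainstem active motor threshold both require MEPs above 50 microvolt "in at least 5 of 10 successive stimuli".
- **Dependent intensities:** "the TS intensity will be set at 125% of rMT", and the conditioning intensity is derived from the brainstem threshold.

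Under Analytical methods, group differences in the neurophysiological measures are to be analysed by multivariable regression at each assessment.

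**The concern.** An analogue filter placed before a digitiser should remove what the digitiser cannot represent. Here the stated filter passes frequencies well beyond that limit, so everything between 2.5 and 10 kHz would reappear at false frequencies inside the recorded band. One of the two figures is therefore either a misprint or an unsuitable choice.

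The MEP itself is slow and would not be distorted. What matters is noise. A peak-to-peak value is a maximum minus a minimum, so noise pushes it upwards. It does so in both the conditioned and the unconditioned response, and the addition is proportionally larger for the smaller one. A ratio below 1 then moves towards 1, so inhibition is understated, most of all in participants with small ipsilesional MEPs. The 50 microvolt rule is exposed in the same way: a response slightly under the limit can be counted as over it, which would lower the threshold found and so the stimulus intensities set from it.

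**Working it through.** **Inputs from the protocol article:** recording frequency 5 kHz; upper filter corner 10 kHz; peak-to-peak amplitude; CBI as conditioned over unconditioned mean amplitude; threshold limit 50 microvolt. The document gives no figure for noise or for expected MEP size, so there is no result of its own to reproduce.

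**Step 1, the mismatch.**
- Nyquist limit = sampling rate / 2 = 5 / 2 = 2.5 kHz.
- Filter corner / Nyquist limit = 10 / 2.5 = 4.
- Sampling rate needed for a 10 kHz corner: above 2 × 10 = 20 kHz.

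**Step 2, noise admitted, if the noise is white (assumption).**
- Share of noise power above the Nyquist limit = 1 − 2.5/10 = 75%.
- Noise RMS relative to a 2.5 kHz corner = √(10/2.5) = 2.
- Noise RMS relative to a 2 kHz corner = √(10/2) = 2.24.

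**Step 3, effect on the measures, by simulation.** Assumptions: white noise with the stated RMS over 10 Hz to 10 kHz; fourth-order band-pass; samples kept at 5 kHz; peak-to-peak taken in a 30 ms window around a model biphasic MEP; unconditioned MEP of 500 or 100 microvolt; true CBI 0.60. The model MEP has 99.9% of its power below about 180 Hz, so the response itself is not aliased. Each cell shows the 10 kHz corner first and the 2 kHz corner second, at the same noise density.

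| Noise RMS over 10 kHz (microvolt) | Mean noise-only peak-to-peak (microvolt) | Noise alone above 50 microvolt | True 40 microvolt MEP read above 50 | CBI, 500 microvolt MEP | CBI, 100 microvolt MEP |
|---|---|---|---|---|---|
| 1 | 5 / 2 | 0% / 0% | 0% / 0% | 0.601 / 0.600 | 0.609 / 0.603 |
| 2 | 11 / 5 | 0% / 0% | under 1% / 0% | 0.603 / 0.601 | 0.620 / 0.607 |
| 5 | 27 / 12 | 0% / 0% | about 87% / 1% | 0.609 / 0.603 | 0.655 / 0.622 |
| 10 | 53 / 24 | about 70% / 0% | about 100% / 72% | 0.620 / 0.607 | 0.708 / 0.648 |

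As a check on the last column at 10 microvolt, the mean amplitudes with the 10 kHz corner were 127.7 microvolt (true 100) and 90.4 microvolt (true 60), and 90.4 / 127.7 = 0.708.

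**Step 4, folding or pass-band?** I kept the 10 kHz corner and the same noise RMS of 10 microvolt, and raised only the sampling rate, so that nothing folds.

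| Sampling rate | Mean noise-only peak-to-peak (microvolt) | CBI, 100 microvolt MEP (true 0.60) |
|---|---|---|
| 5 kHz | 53.5 | 0.708 |
| 24 kHz | 63.7 | 0.732 |
| 40 kHz | 66.3 | 0.737 |

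Removing the aliasing leaves the noise RMS unchanged and makes the peak-to-peak noise slightly larger, because more samples are searched for an extreme. The inflation comes from the wide pass-band. Folding is how that out-of-band noise stays in a 5 kHz record.

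**The case against.** The strongest reply has four parts.

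**The wording leaves room.** The 5 kHz is attached to the biosignal recorder, while a second device digitises. An article may also leave the converter's rate, an anti-alias filter or offline filtering to the full protocol. That stands as a reason to ask before asserting that the data will be aliased. It does not rescue the sentence: either 5 kHz is the sampling rate and the filter does not suit it, or the sentence does not describe the sampling.

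**The size is assumed.** This stands in full. At 1 to 2 microvolt RMS the bias in CBI is at most about 0.02, and with 500 microvolt MEPs it is negligible.

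**A gross threshold failure would be noticed.** A reader might infer that noise alone will satisfy the 50 microvolt rule and give false thresholds. The documents do not support that. In the simulation it did not happen at 1 to 5 microvolt RMS. At levels where it does, the limit would be crossed with no stimulus at all, which an operator would see. What remains is the near-threshold case, where a response a little under 50 microvolt is counted as over it.

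**Aliasing is not the driver.** A reader might also infer that folding inflates the amplitudes, so that faster sampling alone would cure it. Step 4 shows that it would not.

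**Conclusion.** The point holds as an incompatibility between two stated settings. On the natural reading of 5 kHz as the sampling rate, the filter corner is four times the Nyquist limit, and nothing else in the text resolves it. The direction of any bias is clear: MEP amplitudes upwards, a CBI ratio below 1 towards 1, and near-threshold responses more often counted as present.

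Its size is conditional on noise and MEP amplitudes that the document does not give. Under white noise it runs from nothing of consequence (true 0.60 read as about 0.60, 500 microvolt MEPs, 1 to 2 microvolt RMS) to material (about 0.71, against 0.65 with a 2 kHz corner, for 100 microvolt MEPs at 10 microvolt RMS). A 2 kHz corner reduces the bias but does not abolish it.

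It would go too far to say that the trial's CBI results will be biased to an important degree. The point is minor: CBI is an additional neurophysiological assessment, and neither the feasibility criteria nor the ARAT effect size meant for planning the main trial depends on it.

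**What to change.** State the converter's actual sampling rate and low-pass corner, and make them compatible in one of these ways:

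- Set the low-pass corner below half the actual sampling rate, for example 10 Hz to 2 kHz at 5 kHz sampling.
- Or keep the 10 kHz corner, sample above 20 kHz, and apply a digital low-pass filter before any amplitude is measured. Without that last step the noise remains.
- If 5 kHz or 10 kHz is a misprint, correct it. If an anti-alias filter is already in place, say so.

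The cost is one recording setting or a one-line correction, with larger files if the sampling rate is raised. No extra patients, visits or staff are needed. It is best settled before the same set-up is carried into the main trial.
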